## Abstract

**Background:**

The gut microbiome is increasingly recognized as a contributor to disease states. Patients with type 1 diabetes (DM1) have distinct gut microbiota in comparison to non-diabetic individuals, and it has been linked to changes in intestinal permeability, inflammation and insulin resistance. Prebiotics are non-digestible carbohydrates that alter gut microbiota and could potentially improve glycemic control in children with DM1. This pilot study aims to determine the feasibility of a 12-week dietary intervention with prebiotics in children with DM1.

**Methods/design:**

This pilot study is a single-centre, randomized, double-blind, placebo-controlled trial in children aged 8 to 17 years with DM1 for at least one year. Participants will be randomized to receive either placebo (maltodextrin 3.3 g orally/day) or prebiotics (oligofructose-enriched inulin 8 g orally/day; Synergy1, Beneo, Mannheim, Germany). Measures to be assessed at baseline, 3 months and 6 months include: anthropometric measures, insulin doses/regimens, frequency of diabetic ketoacidosis, frequency of severe hypoglycemia, average number of episodes of hypoglycemia per week, serum C-peptide, HbA1c, serum inflammatory markers (IL-6, IFN-gamma, TNF-alpha, and IL-10), GLP-1 and GLP-2, intestinal permeability using urine assessment after ingestion of lactulose, mannitol and 3-O-methylglucose, and stool sample collection for gut microbiota profiling.

**Discussion:**

This is a novel pilot study designed to test feasibility for a fully powered study. We hypothesize that consumption of prebiotics will alter gut microbiota and intestinal permeability, leading to improved glycemic control. Prebiotics are a potentially novel, inexpensive, low-risk treatment addition for DM1 that may improve glycemic control by changes in gut microbiota, gut permeability and inflammation.

**Trial registration:**

ClinicalTrials.gov: NCT02442544. Registered on 10 March 2015.

## Background

The gut microbiome plays a key role in health but is increasingly recognized as a contributor to various disease states when an imbalance or dysbiosis occurs. Both animal and human studies found a difference in microbial composition between those that develop type 1 diabetes from those that did not develop diabetes [1]. In animal studies, interventions that change the gut microbiota can alter immune response and can play a role in the development of type 1 diabetes [2]. In children with type 1 diabetes (DM1), alterations in gut microbiota have been identified [3–6]. For example, bifidobacteria have previously been found to negatively correlate with beta-cell autoimmunity in Finnish children with diabetes-related autoantibodies [3] and in Spanish children with DM1 [6]. *Faecalibacterium prausnitzii*, a butyrate-producing bacterium, has been shown to have some anti-inflammatory effects and has been found to be decreased in children with diabetes-related autoantibodies [3].

Prebiotics are defined as selectively fermented ingredients that result in specific changes in the composition and/or activity of the gastrointestinal microbiota, thus conferring benefit(s) upon host health [7]. Prebiotics have been shown to increase the abundance of both bifidobacteria and *Faecalibacterium prausnitzii* [8] and, therefore, may help correct defects in the gut microbial environment associated with DM1 development and progression. Beyond reducing dysbiosis in the gut microbial environment, prebiotics have also been shown to improve glucose tolerance via mechanisms that likely include enhanced production and secretion of the incretin glucagon-like peptide 1 (GLP-1) [9]. Indeed, prebiotics improved hemoglobin A1c (HbA1c), postprandial glycemic excursion and inflammatory markers in patients with type 2 diabetes [9, 10]. To date however, there have been no studies examining the effect of using prebiotics to alter gut microbiota and intestinal permeability in children with DM1 and whether such changes can improve glycemic control.

In addition to increased incretin production, prebiotics may improve glycemia through its action on intestinal mucosal barrier function and gut microbiota [11–14]. Both animal and human studies have linked gut microbiota to metabolic dysregulation. Patients with diabetes have distinct gut microbiota in comparison to healthy individuals [3, 4], with a higher gram-negative to gram-positive bacterial ratio and a lower abundance of bifidobacteria, an important microbial population with many health benefits [1, 15, 16].

In animal studies, diabetes is also associated with increased gut permeability, allowing bacterial lipopolysaccharides (LPS) from gram-negative bacteria to translocate into the systemic circulation, causing metabolic endotoxemia, triggering pro-inflammatory cytokine secretion and insulin resistance [17–19]. Animal studies showed that prebiotic treatment dose-dependently increases bifidobacteria [20], reduces gut permeability and endotoxemia [21, 22] and improves glucose tolerance [23]. Indeed, bifidobacteria abundance negatively correlates with serum LPS, fasting insulin and glucose [21]. Prebiotics also enhance GLP-2 production, which restores tight junction protein expression and reduces gut permeability [18]. Hence, prebiotics may improve glucose homeostasis by two separate mechanisms: (1) up-regulating GLP-1 to improve beta-cell mass and function, and (2) altering gut microbiota and permeability to a less pro-inflammatory phenotype, improving insulin sensitivity. In humans, bacterial endotoxin activity has been shown to be associated with insulin resistance [24]. However, direct manipulation of gut microbiota in humans and its impact on gut permeability and glycemic control has not been studied, and whether these mechanisms also operate in humans is unknown.

Prebiotics are a potentially novel, inexpensive, low-risk treatment addition for DM1 that may improve glycemic control by changes in gut microbiota, gut permeability and inflammation. This pilot study will provide critical proof of concept data for future trials looking at the efficacy of using prebiotics as an adjunct in the management of DM1 to improve glycemic control.

The primary objective of this study is to determine the effect of a 12-week dietary intervention with 8 g/day of prebiotic intake compared to placebo on glycemic control as measured by HbA1c in children diagnosed with DM1 for at least one year. The secondary objective is to determine the gut microbiota composition in children diagnosed with DM1 consuming prebiotic versus placebo. Further, we aim to examine the differences in gut permeability, serum inflammatory markers, glucagon-like peptide 1 (GLP-1) and GLP-2 and C-peptide in children diagnosed with DM1 consuming prebiotics versus placebo and to assess for diabetes-related adverse reactions (i.e. severe hypoglycemia and diabetic ketoacidosis) associated with use of prebiotics in children with DM1.

## Methods/design

### Design

This pilot study is a single-centre, randomized, double-blind, placebo-controlled trial of prebiotic treatment on gut microbiota, intestinal permeability and glycemic control in children aged 8 to 17 years who have had DM1 for at least one year. A schematic of the study design is given in Fig. 1.

**Fig. 1 Fig1:**
[figure not shown]
CONSORT flow diagram

### Centre and patient selection

Patients will be recruited from the diabetes clinic at the Alberta Children’s Hospital located in Calgary, Alberta, Canada. This is a tertiary care hospital that provides diabetes care to approximately 900 children with DM1. The inclusion and exclusion criteria are outlined in Table 1.

**Table 1 Tab1:** Participant inclusion and exclusion criteria

Inclusion criteria	Exclusion criteria
• Age 8 years to 17 years (inclusive)	• Any hemoglobin A1c greater than 10 % in the previous 6 months
• Diagnosed with type 1 diabetes for at least 12 months	• Chronic medical condition that could affect gut microbiota (examples: Crohn’s disease, cystic fibrosis, irritable bowel syndrome, etc.)
• Followed at the Alberta Children’s Hospital diabetes clinic (Calgary, Alberta, Canada)	• Receiving medications or supplements that could affect gut microbiota (examples: antibiotics, probiotics, prebiotics, laxatives, etc.)
• Parent or legal representative of the patient is willing to give consent for the study and child assents	• Positive celiac disease screen

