### Randomization

Participants will be randomized via computer-generated numbers to intervention or placebo control in a 1:1 ratio. The intervention and placebo groups will not be matched (e.g. age, duration of T1DM, etc.). An investigator not involved in running the study will prepare the randomization sequences and have the random allocation sequence in numbered envelopes in a secure location that will be opened only once a participant has consented and enrolled in the study. The participants, trial coordinator and research staff who enroll the patients will remain blinded to the participants’ group assignment. Participants will be asked at the end of the study to which group they believed they were assigned.

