### Analysis

Analysis will be performed using SPSS 22.0 software (IBM, New York, USA). Results will be considered statistically significant if *p* ≤ 0.05. Baseline descriptive data between the control and intervention group will be compared using chi-square for categorical variables and *t* tests for continuous variables. The primary outcome of HbA1c will be expressed as mean HbA1c values with standard deviations, and a two-sided *t* test will be used to compare HbA1c between placebo and prebiotic groups. Differences between the placebo and prebiotic groups’ C-peptide, inflammatory markers (IL-6, IFN-gamma, TNF-alpha, and IL-10), GLP-1, GLP-2 and intestinal permeability will be compared using a two-sided *t* test. Adverse events will be presented as the proportion of each event seen in each group (placebo and prebiotic). An intent-to-treat analysis will be used with the last data point carried forward for missing data. A secondary analysis will also be performed on a per-protocol basis with all subjects who have completed the intervention and are reported to be compliant with ≥80 % of the prebiotic or placebo packets consumed.

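### C-peptide is compared by an unadjusted t test over all children, so if many are at the assay floor the test loses substantial power and a null result says little about the beta-cell mechanism

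*Protocol article*

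**What the plan says.** - **Entry.** Table 1 (Centre and patient selection) asks for "Diagnosed with type 1 diabetes for at least 12 months" and "Age 8 years to 17 years (inclusive"). It lists no maximum duration and no C-peptide criterion, so only age limits how long a child may have had diabetes.
- **Balance.** Under Randomization: "The intervention and placebo groups will not be matched (e.g. age, duration of T1DM, etc.)". No stratification is described.
- **Mechanism.** The Background proposes two routes to better glycaemia. The first is "up-regulating GLP-1 to improve beta-cell mass and function". The second runs through microbiota, permeability and insulin sensitivity.
- **Status of C-peptide.** After HbA1c (primary) and microbiota (secondary), the objectives add: "we aim to examine the differences in gut permeability, serum inflammatory markers, glucagon-like peptide 1 (GLP-1) and GLP-2 and C-peptide". C-peptide is measured at baseline, 3 and 6 months.
- **Test.** The Analysis section states: "C-peptide, inflammatory markers (IL-6, IFN-gamma, TNF-alpha, and IL-10), GLP-1, GLP-2 and intestinal permeability will be compared using a two-sided" t test. It names no transformation, baseline term or subset for C-peptide. The analysis set is all randomised children: "An intent-to-treat analysis will be used with the last data point carried forward for missing data".

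The section does not say whether levels or changes from baseline are compared. I read it as levels, as it describes for HbA1c. A comparison of changes would use the baseline in part, and the figures below would differ.

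**The concern.** A child with no measurable C-peptide at baseline and at follow-up carries almost no information on a beta-cell effect but still enters the arm mean. If enrolled children range from one year of diabetes to many, C-peptide may form a cluster at the floor plus a skewed tail. An untransformed t test handles that shape poorly. Because the arms are small and unmatched on duration, chance imbalance in the number of secretors could also create a difference or hide one.

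The Background presents the pilot as proof-of-concept for later trials. Under the stated test, a null C-peptide result could not separate an absent beta-cell effect from a sample with few children able to show one. Baseline C-peptide would help with both problems and is already collected, but the stated comparison does not use it.

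**Working it through.** **The plan's own power figure.** It concerns HbA1c only. With 12 completers per arm, SD 1.3, two-sided alpha 0.05 and 80% power, the detectable difference is (1.960 + 0.842) × 1.3 × √(2/12) = 1.49, stated as 1.5. It reproduces. Nothing comparable is given for C-peptide.

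**Inputs for C-peptide.** From the Internal pilot section: 15 per arm enrolled, 12 completing. Everything else is assumed, because the document gives no C-peptide mean, SD, effect, assay limit or share at the floor:
- a share q of children at the floor at every visit, 30% to 80%;
- log-normal C-peptide in the rest, log-SD 0.7;
- a true doubling with prebiotic among those who secrete;
- for the adjusted analysis, a baseline to follow-up correlation of 0.8 on the log scale among secretors.

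**Simulated power, 15 per arm** (ranges are over repeated runs):

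| Share at floor | Planned t test, all children | Log-scale t test, detectable at baseline only | Log scale, all children, baseline-adjusted |
|---|---|---|---|
| 30% | 30–32% | 54–56% | 87–88% |
| 60% | 12% | 31–33% | 53–57% |
| 80% | 4% | 12% | 18% |

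With nobody at the floor, the planned test has about 65% and a log-scale t test about 75%. So at the same sample size, a 60% floor share takes the planned test from 65% to 12%. With 12 per arm and 60% at the floor, the planned test has 8–9% and the subset test 25–27%.

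**Sensitivity of the adjusted analysis.** I changed one input at a time in the same simulation.
- At a baseline correlation of 0.5, power is 54%, 29% and 9% at the three floor shares. That is still above the planned test, but no better than the subset.
- With the log scale but no baseline term (floor value one twentieth of the secretors' median), power is only 12%, 8% and 5%. The baseline term is therefore essential; a log transformation of all children alone does not help once many are at the floor.

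**A second model.** Here the effect is expressed in SD units among secretors, with coefficient of variation 0.6 and 12 per arm. At 1.15 SD (1.5/1.3, the standardised effect of the HbA1c calculation), power of the all-child t test is 77% if every child secretes, 33% if 75% do, 16% if 50% do, 8% if 30% do and 5% if 20% do. At the full-trial size of 107 per arm and an effect of 0.8 SD, it is 93%, 64% and 23% at 75%, 50% and 20% secreting.

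**Can the subset analysis be run?** At 80% at the floor, each child is detectable with probability 0.2. The chance that an arm of 15 has fewer than two detectable children is 0.8¹⁵ + 15 × 0.2 × 0.8¹⁴ = 0.035 + 0.132 = 0.167. For at least one of two arms it is 1 − (1 − 0.167)² = 31%. With 12 per arm: 0.069 + 0.206 = 0.275, and 1 − (1 − 0.275)² = 47%. The subset is therefore unsafe as the main comparison.

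**The case against.** The strongest objection is that the premise is not in the document. No section gives a C-peptide distribution, an assay limit or the duration mix of the clinic. This stands: the point is conditional, and the loss shrinks as the floor share falls below 30%.

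Second, C-peptide is a further aim of a feasibility pilot, no power is claimed for it and no stated decision depends on it. Even with every child secreting, 12 per arm gives only 22% and 47% power for effects of 0.5 and 0.8 SD, so small numbers explain much of the weakness. This stands too, and it lowers the priority.

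Third, transformation, detection limits and subsets are often left to a full protocol or analysis plan, which is not shown. This stands in part. The article does not merely omit detail, however: it names a test, and that test as written makes no use of the baseline value.

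A reader might also go further in two ways that the text does not support:
- **That the C-peptide test is the sole or formal test of the beta-cell mechanism.** The document never says so. GLP-1, the upstream step of that mechanism, is also measured and compared.
- **That the missing maximum duration is an eligibility error.** Entry serves the primary HbA1c aim, and no need for residual secretion is stated for the second mechanism.

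**Conclusion.** The concern holds conditionally and is of low priority. If an appreciable share of children is at the assay floor, the stated comparison loses substantial power, and a null result could not be read as evidence against the beta-cell mechanism in the Background.

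A reader might infer that the test has near-zero power. That cannot be derived from the document. In the main simulation it appears only at the top of the assumed range (4% at 80% at the floor, against 30–32% at 30%), and at the full-trial size power is often far from zero.

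The direction of the loss holds in both models. Its size rests on the assumed floor share, effect, spread and baseline correlation. The HbA1c comparison is not affected.

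**What to change.** In the Analysis section, replace the C-peptide t test with the following:

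1. Compare C-peptide between arms on the log scale in all randomised children, adjusted for baseline C-peptide. Set values below the assay limit, at any visit, to one pre-specified value.
2. Add a pre-specified supportive analysis in children with detectable C-peptide at baseline. Run it only if each arm reaches a minimum number of such children, fixed before unblinding. The subset is defined before treatment, so the randomised comparison within it is kept.
3. Report the number of children with detectable C-peptide by arm and visit.
4. State that a null result does not count against the beta-cell pathway when few children have residual secretion.

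The cost is slightly more analysis work, a model in place of a t test, some dependence on the substituted value, and a supportive subset that may be too small to analyse. No new data are needed. Entry criteria and the HbA1c analysis are unchanged. The change does not make the pilot well powered for C-peptide: at 80% at the floor, the adjusted analysis still has only about 18% power with 15 per arm, or 9% if the baseline correlation is 0.5.

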### Patient recruitment

Patients will be approached during their regular diabetes clinic visits to participate in this study. Posters and information pamphlets will be available so that families can contact the research team if they are interested in participating. Patients will be assessed for eligibility and written informed consent, and where appropriate, assent will be obtained for all study participants.

### Randomization

Participants will be randomized via computer-generated numbers to intervention or placebo control in a 1:1 ratio. The intervention and placebo groups will not be matched (e.g. age, duration of T1DM, etc.). An investigator not involved in running the study will prepare the randomization sequences and have the random allocation sequence in numbered envelopes in a secure location that will be opened only once a participant has consented and enrolled in the study. The participants, trial coordinator and research staff who enroll the patients will remain blinded to the participants’ group assignment. Participants will be asked at the end of the study to which group they believed they were assigned.

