
### Sample size

#### Internal pilot

The initial pilot study will aim to test the feasibility of a fully powered studied in children with type 1 diabetes. To test feasibility in this pilot study, we will enroll 15 subjects per arm. If we assume a drop-out rate of 20 % (12 subjects completing the study in each arm), power of 80 %, and alpha of 0.05 and a standard deviation of 1.3 for HbA1c, then with the pilot study we would be able to detect a mean difference in the absolute HbA1c of 1.5 between the placebo and prebiotic groups.

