#### Full trial

For the full study, the sample size was calculated for a two-sided *t* test comparing two independent samples. Based on previous follow-up data from the Alberta Children’s Hospital Diabetes Clinic, the mean score of HbA1C at baseline in both groups will be estimated to be 8.4 with a standard deviation of 1.3 for each group. A clinically significant change in absolute HbA1c of 0.5 will be used, as this threshold has been used in previous drug trials to demonstrate effectiveness in diabetes. For a power of 80 % and an alpha of 0.05, the number of subjects needed per arm of the study is 107. If we assume a drop-out rate of 20 %, then approximately 135 subjects per arm of the study will be required in a fully powered study.

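### Neither the allocation nor the primary t test uses baseline HbA1c; adjusting for it would make the 30-child pilot more precise at no cost in patients

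*Protocol article*

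**What the plan says.** **Allocation** (protocol article, Randomization). "Participants will be randomized via computer-generated numbers to intervention or placebo control in a 1:1 ratio". The section adds that "The intervention and placebo groups will not be matched (e.g. age, duration of T1DM, etc"). It names no factor for stratification or minimisation, and HbA1c is not mentioned there.

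**Primary analysis** (Analysis). HbA1c is summarised by means and SDs and compared between the arms with a two-sided t test. No baseline term is stated. Baseline characteristics are compared by chi-square and t tests, but nothing links those tests to the primary comparison.

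**Data** (Glycemic control, inflammatory markers, GLP-1 and GLP-2). HbA1c is measured at baseline, 3 months and 6 months, so the covariate will exist for every child.

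**Size** (Internal pilot). "we will enroll 15 subjects per arm"; 20% drop-out leaves 12 completers in each arm, and "we would be able to detect a mean difference in the absolute HbA1c of 1.5 between the placebo and prebiotic groups".

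**SD and target** (Full trial). Baseline HbA1c is taken to average 8.4, with an SD of 1.3 in each arm. On the target effect, the section states: "A clinically significant change in absolute HbA1c of 0.5 will be used".

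**Eligibility** (Table 1). Any HbA1c above 10% in the previous 6 months excludes the child.

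**The concern.** In a small trial, chance can leave the arms unequal on the variable that best predicts the outcome, which here is very likely the child's own starting HbA1c. A plan can handle this in the design, by stratifying, or in the analysis, by adjusting. This plan states a choice on both and takes neither route.

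The effect on glycemic control is the primary objective, and the Background says that the pilot will supply proof-of-concept data for later trials. If the arms start some tenths of a point apart, a reader of the unadjusted comparison cannot tell how much of the follow-up difference was there at the start. Between-child variation that baseline HbA1c could explain also stays in the error term, so the interval is wider than it need be.

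**Working it through.** **Inputs.** SD 1.3, target 0.5, and 107 and about 135 per arm (Full trial); 15 enrolled and 12 completing per arm, detectable difference 1.5, 80% power, alpha 0.05 (Internal pilot); cap of 10% (Table 1). The documents give no correlation between baseline and follow-up HbA1c, so 0.5 and 0.7 are assumptions.

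**1. The plan's own figures.**
- Full trial: n = 2 × (1.960 + 0.842)² × 1.3² / 0.5² = 106.1, so 107 per arm. 107 / 0.8 = 133.75, so 134, close to the stated 135.
- Pilot: (1.960 + 0.842) × 1.3 × √(2/12) = 2.802 × 0.531 = 1.49, which matches 1.5. This is the normal approximation; the exact t calculation gives 1.56, and 77.1% power for 1.5.

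**2. Chance of a baseline gap of 0.5 or more.** SE = SD × √(2/n); P = 2 × [1 − Φ(0.5/SE)].

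| Case | SE | P, either direction |
|---|---|---|
| 15 per arm, SD 1.3 | 0.475 | 29% |
| 12 per arm, SD 1.3 | 0.531 | 35% |
| 15 per arm, SD 1.09 | 0.396 | 21% |
| 107 per arm, SD 1.3 | 0.178 | 0.5% |

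The SD of 1.09 comes from truncating a normal distribution with mean 8.4 and SD 1.3 at 10. That is an assumption about how the cap acts. A gap in one given direction has half the probability: about 15% in the first row.

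**3. How much of a gap reaches the result.** With equal SDs at baseline and follow-up, an observed gap d shifts the expected unadjusted follow-up difference by ρ × d. For d = 0.5 that is 0.25 at ρ = 0.5 and 0.35 at ρ = 0.7.

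**4. Gain from baseline adjustment.** ANCOVA multiplies the SE by about √(1 − ρ²). With 12 per arm, the detectable difference becomes:
- ρ = 0.5: 1.49 × 0.866 = 1.29
- ρ = 0.7: 1.49 × 0.714 = 1.06

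These figures ignore a small loss from estimating the slope. With 15 per arm and ρ = 0.7, the formula gives an SE of 0.475 × 0.714 = 0.339, while simulation gives about 0.35, roughly 3% more. The unadjusted SE is 0.475.

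**5. What stratifying would add.** Simulated scheme: two HbA1c strata cut at 8.4, blocks of 2 and 4, SD 1.3.
- The chance of a baseline gap of 0.5 or more falls to 9 to 10% if the stratifying HbA1c equals the study baseline value. If the two correlate at 0.9 or 0.8 (assumed), it falls only to about 14% or 18%.
- Once baseline is in the model, stratifying moves the SE at ρ = 0.7 from about 0.35 to between 0.34 and 0.35, a gain of about 0 to 3%.

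**The case against.** The strongest reply is that nothing here is an error. Unstratified 1:1 randomisation is a valid design, openly disclosed. Over repeated randomisations, chance gaps do not bias the difference in means, the t test keeps its type I error, and the SD of 1.3 used for power already contains this variation. All of that stands. The point concerns efficiency and readability.

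Four stronger readings are tempting, and the documents do not support them.

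- *A 3 in 10 chance of a misleading trial.* The 0.5 threshold is set for the full trial, whereas the pilot is sized for 1.5. A baseline gap of 1.5 or more with 15 per arm has a probability of only 0.16%. The 29% also counts both directions and uses an SD that the eligibility cap probably reduces. It mainly reflects the small sample.
- *A gap passes whole into the result.* It passes only in proportion to the correlation (step 3).
- *The 15 per arm is not secured.* That would follow only from an unrestricted list. The article does not say whether the list is blocked, and a condensed article may leave that out; saying that the groups are not matched does not settle it. Even a 12:18 split gives an SE of 1.3 × √(1/12 + 1/18) = 0.484, 2% above 0.475.
- *The allocation list must be changed.* The Trial status section says that recruitment has begun, and step 5 shows how little stratifying adds after adjustment.

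It may also be said that adjustment belongs in an analysis plan that is not shown. But the article does not leave the primary test open: it names an unadjusted t test.

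**Conclusion.** The concern holds as a matter of precision and interpretability, and the weakness to act on is the unadjusted primary comparison. Baseline HbA1c is measured but used in neither allocation nor primary analysis. The chance of a starting gap of 0.5 or more is about 29% on the stated SD, or about 21% if the cap acts as assumed. Ignoring baseline HbA1c leaves the detectable difference with 12 per arm at 1.49, where about 1.29 or 1.06 could be had. Those two figures rest on assumed correlations of 0.5 and 0.7 and on the normal approximation; a weaker correlation would bring less.

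A reader might infer that the allocation is faulty or the trial biased. Neither follows. Unstratified allocation is acceptable here, and preferring a stratified list is a matter of taste once the analysis uses baseline.

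**What to change.** In the Analysis section, replace the two-sided t test for the primary outcome with an ANCOVA: follow-up HbA1c on arm, with baseline HbA1c as a continuous covariate, reporting the adjusted difference with its 95% confidence interval. Fix this before unblinding so that the covariate is not chosen in the light of the baseline tests. The t test can stay as a supportive analysis. If a separate analysis plan already adjusts for baseline, bring the protocol text into line with it.

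The cost is a short amendment and one degree of freedom. It needs no extra patients, visits or staff, the HbA1c value is already collected, and children already randomised are unaffected.

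Optional only: the independent investigator could issue lists in random blocks of 2 and 4 within two strata of the latest clinic HbA1c (below, or at or above, 8.4) for children not yet randomised, leaving earlier allocations as they are. This improves the look of the baseline table more than the precision of the adjusted estimate.
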